#### Evaluation of school lunch by teachers and support staff

Teachers and support staff’ perceptions of child’s eating and drinking behavior during school lunch will be assessed two times (T1 and T2) by a questionnaire with three-point Likert agreement scales (disagree, neutral, agree) to indicate the level of disagreement or agreement to the statements ‘Children generally like the lunch’, ‘Children have enough time to eat’, ‘Children find it cozy during lunch’, ‘There is sufficient of everything’, ‘Lunch is ready on time’, ‘Lunch is cleaned up on time’, ‘The atmosphere is good during the lunch’, and ‘The atmosphere in class is good during the afternoon’. Teachers could also indicate ‘not applicable’. These items were informed by previous research on the introduction a healthy school lunch in the Netherlands [16, 26].

### Data analysis

#### Consumption and evaluation of lunch by children

The unit of analysis will be the child. The primary outcome measures of this study is the food and drink consumption of the children during lunch, which is measured by analyzing photographs of the lunch of each child. Vegetable portion size in grams will be estimated based on the pictures and observation forms. Bread will be reported in type of bread and slices, crackers and fruit in pieces and drinks in milliliters. Of all products, intake will be assessed by subtracting the portion after from the portion before and tested for statistically significant differences. Important outcomes will be the incidence of children consuming a particular product. Success of the intervention will be indicated by at least 50% of the children consuming at least a portion of 25 g of vegetables during lunch.

The number of different products per lunch will be calculated. Next, the share of healthier ‘Wheel of Five’ products consumed will be plotted and compared across time using chi-square analyses and correlations. Acceptability of the school lunch is assessed by the questionnaire item ‘the lunch was tasty’ assessed at T1 and T2. Adequate acceptability will be indicated by 75% of the children reporting a mean rating of three or higher.

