### Dietary intervention

The dietary intervention consist of an ad-libitum self-served school lunch in the intervention schools during a 6-month period. The school lunch will be developed to be nutritionally balanced and tasty.

About 80% of all available options per week will be healthy choices according to the Dutch Nutritional Guidelines based on their levels of saturated and trans fat, added sugar, salt, dietary fibre, and energy density [20]. The daily basis of the lunch is whole-grain bread slices with sandwich fillings. Every day, raw (snack) vegetables will be provided (50 g per child per day). In addition, there will be a special lunch item, such as a vegetable soup, fruit or a boiled egg every day. In two of the three schools, there will be no lunch at Wednesday as children go home early in the afternoon.

Two lunch menus are developed for three weeks that will be repeated in a three month cycle. A dietician and nutritionist will be involved to create the menu. The menus will be inspired by a qualitative study among children, parents and school staff [21], experts and chefs who provided input during workshops to make sure that the lunch options are healthy, varied and tasty. Religious or allergy-related restrictions will be taken into account. Teachers or support staff will be trained to order foods each week in a specially developed ordering system. In consultation with the school it will be determined how the lunch is organized logistically and practically. This is possible, for example, with volunteers such as parents or support staff who are already working at school. Members of the research team will visit schools regularly to provide support on this process. In case a product will be disliked by a large number of children even after repeated exposure, it will be replaced by another product. This will be decided based on these school visits by members of the research team.

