Children consume the lunch in the classroom, which is similar to where they eat their current packed lunch from home. During the intervention, all children receive a cup and a lunch box that can be used as a plate to eat from during lunch. Children bring this lunch box and cup home to be cleaned and bring it back to school the next day. Equipment such as a fridge and serving plates to be put in school or classroom will be bought by the project team if needed. Children will be able to select lunch with food of high nutritional value by walking along a buffet at which all options are displayed. The buffets are displayed in the class room (one school) or in a central place in the school (two schools). Teachers are free to organize distribution in different ways, for example by putting products at groups of desks. Ideas and inspiration for healthy toppings on bread will be provided to the children by means of printed placemats and posters that will be displayed during lunch. Children are still allowed to bring a lunch item from home if they would like. Responsible school staff will receive instructions on how to deal with food safety by visits of the research team.

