### Outcome measures

#### Consumption and evaluation of lunch by children

At baseline, lunch intake data of vegetables, bread, toppings, drinks and additional products (e.g. snacks) will be collected as primary outcome measures within one month before start of the school lunch. To assess lunch intake at school, the lunch of each child will be photographed just before and after consumption, and lunch components will be noted on an observation form. At baseline, children will be asked to open their lunch box and drink cup so that the products can be photographed. For different classes and schools this will be done at different weekdays to capture the variation in food offerings. Each product in the lunch box and drink cup will be classified on its healthiness by using the criteria of the Dutch nutrition guidelines: fit within recommended Wheel of Five, weekly choice or daily choice. We consider the food groups ‘vegetables’, ‘whole grain bread’ and ‘milk products and tea without sugar’ as healthy, given that they are included in the Wheel of Five, the Dutch national counselling model based on their association with a reduced risk for chronic diseases. Food groups which are advised to be limited are considered unhealthy, such as processed meats and sugar sweetened beverages [22]. For all the products, an estimation of consumption amounts will be made based on the pictures and an observation form [23]. No software will be used to determine portion size. Observers record the type of drink present and also provide an estimation of the portion size (i.e. about 200, 300, 500 ml), number of bread slices with topping present, margarine or butter spread. This measure will be repeated at T1 (after three months) and T2 (after six months, see also Table 1).

**Table 1 Tab1:** Overview of included outcome measures (children)

Outcome measures	Time of measurement	T1 (after 3 months)	T2 (after 6 months)
	Baseline T0		
*Primary outcome measures child*			
- Lunch intake: observation by photographing lunch with questionnaire among children	X	X	X
*Secondary outcome measures child*			
- Evaluation and satiation after lunch: questionnaire among children	X	X	X

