The secondary outcome measures for children will be collected by means of a questionnaire and involve their evaluation of the lunch and the post-lunch satiation they experience. The evaluation of the school lunch was added by the item ‘The lunch was tasty’ and ‘We had a good time during lunch’ (5-point scale). An item was included to assess the time to eat the lunch: ‘I had enough time to eat’. Response categories will be depicted via smiley faces. After introduction of the school lunch, the following items will be added to evaluate the school lunch ‘there is enough choice at lunch’, ‘I like it to prepare my own sandwich in class’, and ‘I prefer to bring my own sandwiches from home’.

To assess children’s evaluation of the quantity of lunch consumed, children will be asked the question ‘How much did you eat’ with three answer categories: ‘too little’, ‘sufficient’ and ‘too much’. To measure overall satiation after lunch, we use the specifically designed measurement instrument of Faith and colleagues [24] who use an ordinal silhouette scale with increasing numbers of circles in the stomach region to indicate increasing levels of fullness.

In the follow-up questionnaire, children will provide their age, gender and ethnicity. Children will complete the survey on their own in the classroom after lunch. Questionnaires will be administrated using EyeQuestion software at Lenovo tablets. A similar data collection procedure will take place after three months (T1) and six months (T2). At those time points, questions will be added about whether they have eaten the products of the lunch menu and their evaluation of these products.

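### Before-minus-after scoring suits the packed lunch at T0 but makes no provision for later helpings from the ad libitum lunch at T1 and T2, so follow-up amounts may be under-counted

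*Protocol article*

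**What the plan says.** The protocol article (Data analysis, consumption and evaluation of lunch by children) states the scoring rule: "Of all products, intake will be assessed by subtracting the portion after from the portion before". The matching part of Outcome measures sets the time points and the second record: "the lunch of each child will be photographed just before and after consumption, and lunch components will be noted on an observation form". It adds that "an estimation of consumption amounts will be made based on the pictures and an observation form", and describes the observer's task thus: "Observers record the type of drink present and also provide an estimation of the portion size", together with the bread slices, topping and spread present. At baseline the child opens the lunch box and cup for the photograph. The measure is then repeated at T1 and T2, with no change described for the new setting.

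The setting does change. Under Dietary intervention: "The dietary intervention consist of an ad-libitum self-served school lunch in the intervention schools". Food comes from a buffet, in the classroom at one school and in a central place at two. In addition, "Teachers are free to organize distribution in different ways, for example by putting products at groups of desks".

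Two results depend directly on the amounts: the intake of each product, and the success criterion that half of the children eat 25 g of vegetables or more at lunch.

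**The concern.** Before minus after equals intake only if the first portion holds everything the child will go on to eat. A packed lunch meets that condition. A lunch with no set limit, with food still available after the first photograph, need not: a second sandwich, a return to the buffet or vegetables picked up at the desk group would enter only the second photograph, and only as leftovers.

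An error of this kind would be tied to the visit, little or none at T0 and possibly appreciable at T1 and T2, so it would enter the comparison over time directly. It could also differ between schools and classes, because the way food is distributed differs. The 25 g criterion is the most exposed result, since it turns an amount into pass or fail at a fixed cut.

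**Working it through.** **The rule in symbols.** For one child and one product, let F be the portion at the first photograph, A the amount taken afterwards, L the leftovers at the second photograph, and R the amount returned or passed to another child (so not in L).

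- True intake = F + A − L − R
- Scored intake = F − L
- Error = scored − true = R − A

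At T0, A and R are close to zero unless children swap food. At T1 and T2 the score is too low whenever A exceeds R. The error is the whole amount taken later, not only the part eaten.

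- F = 15 g, A = 15 g, L = R = 0: true 30 g, scored 15 g. The child passes the 25 g mark but is scored below it.
- F = 15 g (all eaten), A = 15 g (all left, so L = 15 g), R = 0: true 15 g, scored 0 g.
- F = 30 g, A = 0, R = 10 g, L = 0: true 20 g, scored 30 g. Here the error runs upward.

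The gram values are invented to show the mechanism.

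**The plan's own sample size.** The article gives 134 children to detect 13.4% against a population rate of 6.7%, two-sided alpha 0.05, power 0.80. The one-sample formula [1.96·√(0.067·0.933) + 0.842·√(0.134·0.866)]² / 0.067² gives 134.4, which agrees. This point does not dispute that figure; 134 is used below only as a working sample size.

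**Effect on the 50% criterion.** The documents give neither a refill rate nor an expected share reaching 25 g, so both are assumptions shown over a range. Let t be the true share reaching 25 g and m the fraction of those children scored below 25 g because of later helpings. The expected observed share is t(1 − m). The probability of observing at least 67 of 134 is binomial, ignoring clustering.

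| True share t | m = 0 | m = 5% | m = 10% | m = 20% |
|---|---|---|---|---|
| 50%: observed (probability) | 50% (0.534) | 47.5% (0.311) | 45% (0.141) | 40% (0.012) |
| 55%: observed (probability) | 55% (0.894) | 52.25% (0.729) | 49.5% (0.488) | 44% (0.095) |
| 60%: observed (probability) | 60% (0.992) | 57% (0.957) | 54% (0.845) | 48% (0.353) |

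The expected verdict turns when m exceeds 1 − 50/t: 9.1% at t = 55%, 16.7% at 60%, 23.1% at 65% and 37.5% at 80%. If t is below 50%, under-counting does not change the expected verdict.

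**Any-intake incidence.** A yes/no outcome is scored wrongly only if none of the product was in the first serving or, less plausibly, if leftovers from a later helping equal or exceed the first portion. If a fraction m of vegetable eaters were lost in this way, power at 134 children and a true 13.4% would be 0.80 at m = 0, 0.73 at 5%, 0.66 at 10% and 0.47 at 20%. The relevant m should be smaller here than for the 25 g cut.

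**The case against.** The strongest reply is that this is a condensed article. How an observer logs a second helping is field procedure, and the article does not forbid adding it to the portion before. Amounts rest on the observation form as well as the photographs, and at T1 and T2 children are also asked whether they ate the menu products. Vegetables are supplied at 50 g per child per day, which limits average refills. The questionnaire item "I like it to prepare my own sandwich in class" does not show that sandwiches are made after the first photograph. If under-counting did dominate, it would work against the hypothesised rise in vegetable intake and would not create a false success.

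Much of this stands, and it limits the claim. It does not remove it. The article does more than leave a detail out: it states a formula and carries it into a setting where, followed exactly, it can give the wrong amount. The form is described as recording what is present, and later helpings are not named. The children's questions have no stated amounts and so cannot settle grams or the 25 g cut. A supply of 50 g per child is compatible with 15 g taken first and 15 g later. A bias against the hypothesis still matters, because a useful lunch could be judged a failure, and less healthy items taken later would be under-counted too.

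A reader might infer that later helpings certainly are missed, that the error can only run downward, that follow-up amounts are therefore lower bounds, and that failure on the 50% criterion should never be declared from these data. The documents do not support this. They are silent on how often children took more and on what the forms captured. Returned or passed-on food is scored as eaten, which pushes the other way.

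**Conclusion.** The scoring rule, as written, does not fit the ad libitum lunch. It leaves out helpings taken after the first photograph and subtracts their leftovers, so T1 and T2 amounts and the 25 g result may be too low relative to baseline. Under-counting is the likely direction but not a certain one, and any-intake incidence is less affected.

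The size cannot be derived from the documents. The figures above rest on assumed true shares and missed fractions, on 134 children and on no clustering. They show that the 50% verdict is fragile when the true share lies a little above the cut (9.1% missed is enough at 55%) and robust when it lies well above (37.5% is needed at 80%). The point calls for a corrected definition and a sensitivity analysis. It does not justify discarding the criterion or making it one-sided.

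**What to change.** Define intake at T1 and T2 as the first portion plus all added portions minus leftovers, and count food returned or passed on as not eaten by that child. Record added, returned and passed-on items on the existing observation form, or by an extra photograph, including in classes where products stand at groups of desks.

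The Study status section says that data collection ended in April 2019 and that analysis is under way. For those data:

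- Check whether the forms or photographs captured added servings and, if they did, use the definition above.
- If they did not, report T1 and T2 amounts and the 25 g result by distribution mode (classroom buffet, central buffet, desk groups).
- State the likely under-count as a limitation, noting that returned or passed-on food could offset it.
- Show how the 50% verdict changes over a range of assumed missed fractions, as in the table above.

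The cost for a future round is a little more recording by observers who are already present. For this study it is a check of existing records, a change of wording, results split by distribution mode and one sensitivity table.

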## Methods

### Study design

In the Healthy School Lunch project children in grades 5–8 (aged 8–12 years) of three primary schools in the Netherlands will receive a healthy school lunch for a 6-month period (November 2018 to April 2019). The development of this healthy school lunch is guided by a study among parents and children about desired school lunch concepts [16, 17]. Important to note is that in the Netherlands, it is very common for children to take all their foods and drinks from home (morning snack and lunch). There is no opportunity to buy food or drinks at primary school and there is no national subsidized school lunch program which offers school meals. Most primary schools in the Netherlands report to have a written food policy (e.g. on what is allowed to bring) although there is no legal obligation to do so [18].

To answer research question 1, we will collect lunch consumption data by means of pictures. All intervention group children will have to complete an initial baseline measurement in the situation where they still bring their own packed lunch. They will also have to complete a second and third follow-up questionnaire at month 3 half-way and month 6 at the end of the period in which a healthy school lunch will be provided.

To answer the second research question, a quasi-experimental, intervention-comparison group design (3 intervention schools and 3 comparison schools) will be carried out. There will be no randomization of the intervention and comparison schools, as the schools had to fully agree and decide on their participation beforehand, which required consent from their stakeholders (teachers, parents, support staff). Potential compensation effects will be measured with a single brief questionnaire among parents both at the three intervention schools and at the three comparison schools at month 6 of the lunch period. The school lunch will also be evaluated by parents (discussion groups) and teachers and support staff (brief questionnaire).

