### Recruitment

A convenience sample of three primary schools agreed to participate in the intervention condition. Initial contact was established with more than 20 schools in different parts of the Netherlands, particularly focused on Amsterdam and Ede. Schools were contacted by members of the research team to recruit them for the study. In addition, a presentation was conducted for interested school personnel at a regional meeting for school directors. Recruitment of schools was based on pragmatic reasons. Inclusion criterion was having a continuous time schedule, where children lunch at school.

A power calculation was conducted to determine the sample size necessary to detect changes in the primary outcome variable ‘vegetable consumption’. Only 6.7% of Dutch primary school children eat some vegetables at school during lunch [11]. We calculated the required sample size with a study group incidence of 13.4% of children eating some vegetables (doubling the population incidence of 6.7%). This is a conservative estimate, as for each participating child 50 g of vegetables will be available each day. In the case of doubling the population prevalence, 134 children would be needed in the study sample to reach a required power of 0.8, when the statistical analysis will be performed at the 2-tailed alpha (0.05). This calculation is made using the sample size calculator ClinCalc [19]. To account for the clustered nature of the data (classes in three schools), the need for a proper process evaluation and potential dropouts, more participants are needed.

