Schools were situated in the capital of the Netherlands Amsterdam and in two small cities, i.e. Lunteren and Vlaardingen (10.000–100.000 inhabitants). Two of the three schools are situated in a district characterized by residents with a lower SEP (Amsterdam and Vlaardingen) and one in a semi-rural town with children of parents with a relatively high SEP (Lunteren). Comparison schools were recruited to match these SEP levels. All children of grades 5 till 8 were invited to participate in the study. Children of grades 1 to 4 were not invited. This was done given budget constraints and we expected that older children would be better able to reflect on their experiences in the questionnaire. Children and parents who decided to join the lunch after the start will also be enrolled. Consequently, data at baseline can be missing for these children. Letters will be sent to parents to explain the study and school lunch. At each school, information meetings will be set up to inform all parents and children. All parents of children that participate will be send a letter after about three months with an invitation to give feedback about the school lunch. This evaluation is not part of the measures, but will be used to adapt and improve the intervention if necessary.

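### The healthy-product share is compared over T0, T1 and T2 with chi-square tests and correlations that allow for neither repeated measurement of the same children nor clustering in classes

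*Protocol article*

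**What the plan says.** All references are to the Protocol article.

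- **Test over time.** Under Data analysis, Consumption and evaluation of lunch by children, the share of healthier Wheel of Five "products consumed will be plotted and compared across time using chi-square analyses and correlations". The same section states: "The unit of analysis will be the child".
- **Other intakes.** For each product, "intake will be assessed by subtracting the portion after from the portion before and tested for statistically significant differences". No test is named.
- **Repeated measurement.** Study design: "All intervention group children will have to complete an initial baseline measurement in the situation where they still bring their own packed lunch". Outcome measures, on the lunch photographs: "This measure will be repeated at T1 (after three months) and T2 (after six months, see also Table 1".
- **Clustering.** Recruitment calls for a larger sample, in a sentence that begins: "To account for the clustered nature of the data (classes in three schools), the need for a proper process evaluation and potential dropouts, more participants". This is the only place where clustering appears; the analysis section does not take it up.
- **Late joiners.** Recruitment allows children to enter after the start and adds: "Consequently, data at baseline can be missing for these children".
- **Success rules.** At least half of the children eating at least 25 g of vegetables, and 75% rating the lunch three or higher. Both are thresholds, not tests.

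**The concern.** A chi-square test on a table of outcome by time point treats every observation as a separate independent unit. Here most children contribute up to three observations, and classmates are likely to resemble each other at a given visit. The article recognises the second feature when it discusses numbers, but not when it names the test.

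The design gives classes reasons to move up or down together between visits. Different classes and schools are photographed on different weekdays, a daily special item is offered during the intervention, and teachers may organise distribution in their own way.

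At stake is the only test that the article names for change over time in its primary outcome domain. Its p-values could be too large or too small, and a reader of the results could not tell which. A comparison of whoever is present at each visit can also shift because late joiners differ from the children measured at baseline.

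**Working it through.** **The plan's own figure.** The analysis sentence carries no number. The nearest figure is the 134 children in Recruitment. It reproduces as a one-sample test of 13.4% against a fixed 6.7%, two-sided alpha 0.05, power 0.80:

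n = [1.96·√(0.067·0.933) + 0.842·√(0.134·0.866)]² / 0.067² = 134.4.

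This formula contains no within-child correlation and no design effect, so it gives no input for the check below.

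**Inputs.** The document gives no ICC, within-child correlation or class size. Assumed: m = 22 children per class; within-child correlation ρ = 0.3 (range 0.1 to 0.5); class-by-time ICC from 0 to 0.10. The class-by-time ICC is the extra resemblance of classmates at the same visit over their resemblance across visits.

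**Formula.** For the difference between two time points in N children, an independence test uses variance 2σ²/N. The true variance is that quantity multiplied by

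V = (1 − ρ) + (m − 1)·ICC(class-by-time).

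A class effect that is constant over time cancels from the difference. The true size of a nominal 5% test is 2·[1 − Φ(1.96/√V)].

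**Results at ρ = 0.3, m = 22.**

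| Class-by-time ICC | V | 1.96/√V | True size |
|---|---|---|---|
| 0 | 0.70 | 2.343 | 1.9% |
| 0.01 | 0.91 | 2.055 | 4.0% |
| 0.02 | 1.12 | 1.852 | 6.4% |
| 0.05 | 1.75 | 1.482 | 13.8% |
| 0.10 | 2.80 | 1.171 | 24.1% |

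The two errors cancel when (m − 1)·ICC = ρ, that is at ICC = 0.3/21 = 0.014.

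**Other values of ρ.** Over the same five ICC values, ρ = 0.1 gives 3.9%, 6.3%, 8.8%, 16.0% and 25.8%. With ρ = 0.5 the sizes are 0.6%, 2.0%, 4.1%, 11.5% and 22.4%.

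**Simulation with three time points.** Assumed 12 classes of 22, no true change, a binary outcome at 10% or 50% prevalence, latent child variance 0.3 and constant class variance 0.1, with 5000 runs per setting. Latent variances are not on the same scale as the ICCs above.

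| Latent class-by-time variance | Chi-square, size at 10% / 50% | Correlation with time, size at 10% / 50% |
|---|---|---|
| 0 | 3.3% / 1.8% | 3.5% / 2.2% |
| 0.02 | 5.2% / 5.7% | 5.1% / 5.1% |
| 0.05 | 9.6% / 11.8% | 8.8% / 9.3% |
| 0.10 | 17.6% / 24.0% | 13.8% / 17.9% |

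The pattern is the same. A correlation of the outcome with time does test trend, but it has the same dependence fault. A correlation between the values at two time points is unchanged by a uniform shift, so it does not test change.

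**Late joiners.** If a fraction f of the T2 children joined late and their mean differs by d from the others, the T2 figure moves by f·d with no change in any child. The document gives neither quantity. For illustration, f = 0.2 and d = ±20 percentage points give ±4 points; f = 0.1 and d = ±10 give ±1 point.

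**The case against.** The best defence is that McNemar's test is also a chi-square test, and that for the parent questionnaire the authors specify the independence version while here they do not. So the unpaired reading is an inference. That stands as a caution, but it does not rescue the sentence. McNemar's test compares two time points on a binary outcome, whereas here there are three time points and a share. Cochran's Q would cover three time points, but again only for a binary outcome. Neither allows for classes, and both need children with complete data.

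A second defence is that an article may leave detail to an analysis plan. That would cover an unnamed method. Here a method is named, and it does not fit the stated design.

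Several stronger readings are tempting, and the document does not support them:

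- **That all p-values for the first research question are wrong.** The sentence covers only the Wheel of Five share. No test is named for grams, slices or millilitres, and the success rules are thresholds.
- **That the correlations cannot test change.** This is true between time points but not for a correlation with time. The text does not say which is meant.
- **That the chi-square must count products.** The child is the stated unit, and children could be classified by their healthy share, although no cut-off is given.
- **That every class shares one measurement day and menu.** The text says only that weekdays differ between classes and schools. At T0 children eat their own packed lunches.
- **That the false-positive rate is inflated to about 17%.** That figure uses clustering alone (1 + 21·0.05 = 2.05, size 17.1%). With pairing at ρ = 0.3 it is 13.8%, and at low ICC the test is near nominal or conservative.
- **That late joiners push results upward.** They could be keener or more reluctant; nothing in the text settles the sign.

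**Conclusion.** The point holds for the comparison of the Wheel of Five share over time. The named analysis does not match data from the same children at three visits, grouped in classes, so its p-values cannot be relied on. Under the assumed ρ = 0.3 and 22 per class, the true size runs from 1.9% to 24.1% as the class-by-time ICC goes from 0 to 0.10. It is close to 5% only where the two errors happen to offset each other. Neither the direction nor the size of the error is established by the document. The effect of late joiners is possible, but its size and sign are unknown. The conclusion rests on reading the chi-square as one for independent observations, which is the natural reading because no paired or clustered method is mentioned.

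**What to change.** Replace the chi-square comparison over time with wording such as:

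> The healthy share (number of healthy products out of all products consumed, per child and visit) is analysed with a binomial mixed model or GEE. Time (T0, T1, T2) and school are fixed effects. The model allows for correlation within child and for class-level dependence, including class-by-time, with a small-sample correction for the number of classes. Change from T0 is estimated in children with a baseline measurement; late joiners are added in a sensitivity analysis.

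Three details:

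- The model should also allow for resemblance between products in one child's lunch, through an occasion-level term or a robust variance clustered on class.
- If the proportion of children eating a given product is tested over time, use the same approach with a binary outcome. For rarely eaten products the full set of random effects may not be estimable, and GEE clustered on class is then the simpler choice.
- Drop the correlations as a test of change, or state that they are descriptive and between which variables.

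**Cost.** Only wording and code change. The Study status section says that data collection is complete and analysis is under way, so no new data are needed. Some intervals may be wider and the analysis is slightly more complex. The 50% and 75% criteria stay as they are.
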